### Interventions

2.3

All study groups received albendazole 400 mg, an anthelminthic drug that is highly efficacious against hookworm infection [13]. The only difference between the three study groups is the frequency of treatment, which is outlined in Fig. 2. In order to mimic the population-based MDA campaigns initiated by the GoI for elimination of lymphatic filariasis [29], designated deworming days were planned for each village and the residents informed well in advance. Everyone present in the village, who were otherwise eligible and provided written informed consent, were administered a single dose of albendazole 400 mg through door-to-door household visits. A mop-up campaign was conducted the subsequent day to ensure maximum coverage. Participants were interviewed the subsequent day to record details of tablet consumption, and followed up repeatedly for a period of 1 week post-treatment to record any adverse/serious adverse events following intervention.

### Outcome measures

2.4

The effectiveness of treatment was evaluated qualitatively, based on the prevalence of hookworm infection, and quantitatively based on the intensity of infection (fecal egg count). Prevalence and intensity of infection at the end of 12 months after the last MDA cycle is the primary outcome measure for this study. Secondary outcome measures include prevalence and intensity of infection after each treatment cycle and at 3, 6, and 9 months post-treatment. Long-term effectiveness of the treatment on prevalence and intensity of infection will be assessed through a follow-up cross-sectional parasitological survey 2 years after the last MDA cycle.

### Sample size

2.5

The sample size was calculated based on following assumptions: 38% prevalence of hookworm infection at baseline [27]; CR of 75% [14]; reinfection rate of 60% at the end of 1 year [19] in the single cycle group; a minimum effect size of 30%; power of 80%; alpha error of 5%; and 10% refusal rate. This requires approximately 165 participants in each group [32]. Since this is a cluster randomized trial, the sample size was inflated to account for the increased variance due to clustering of hookworm cases at village and household levels [33]. Analysis of data from two previous cross-sectional studies in Tamil Nadu [27], [34] showed an intra-cluster correlation coefficient of 0.06 for hookworm infection, which translated into a design effect of 2.7 for a cluster-size of 30. Based on this, a total sample size of 450 participants per intervention group (single/two/four cycles) was considered adequate to detect effectiveness of the intervention regimes, both qualitatively and quantitatively. Thus, at least 1350 participants in 45 clusters (30 in each cluster) had to be contacted during each parasitological survey (Fig. 2).

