Baseline stool samples were obtained from a total of 2082 participants, with a median (IQR) number of 46 (44–48) participants per village providing one or more stool samples; 1727 (82.9%) provided all 3 stool samples as per protocol. Three hundred and eighty six (18.5%) of the 2082 participants were positive for hookworm with a mean (SD) intensity of 678 (1649) eggs per gram (epg) of feces. The majority (361, 93.5%) had low intensity infection (<2000 epg) and only 12 (3.1%) hookworm positive individuals excreted ≥4000 epg (high intensity infection).

The socio-demographic profile of enrolled participants from whom baseline stool sample(s) was obtained and those from whom baseline stool sample was not obtained is outlined in Table 3. Comparison of their socio-demographic profile revealed some differences. Participants providing stool samples tended to be younger (*P* < 0.001), were less likely to engage in agriculture-related activities (*P* < 0.001) and attained slightly lower educational levels (*P* = 0.069). They were, however, comparable in terms of gender distribution (*P* = 0.135), socio-economic status (*P* = 0.150), usage of public taps (*P* = 0.693) and toilet usage (*P* = 0.917).

**Table 3 tbl3:** Comparison of socio-demographic characteristics of enrolled participants from whom baseline stool sample was obtained (n = 2082) with those from whom baseline stool sample was not obtained (n = 6599).

	Baseline stool sample		*P*-value^b^
	Obtained	Not obtained	
Age (in completed years)^a^			
<5 year	131 (6.3)	243 (3.7)	<0.001
5–14 year	642 (30.8)	1418 (21.5)	
15–44 year	997 (47.9)	3893 (59.0)	
≥45 year	312 (15.0)	1045 (15.8)	
Gender^a^			
Male	1021 (49.0)	3360 (50.9)	0.135
Female	1061 (51.0)	3239 (49.1)	
Socio-economic status^a^			
Low	423 (20.3)	1393 (21.1)	0.905
Middle	1089 (52.3)	3344 (50.7)	
High	570 (27.4)	1862 (28.2)	
Engaged in agriculture-related activity^a^			
Yes	1120 (53.8)	4003 (60.7)	<0.001
No	962 (46.2)	2596 (39.3)	
Level of education^a^			
No formal schooling	956 (45.9)	3074 (46.6)	0.069
Primary school (1–5 years)	583 (28.0)	1388 (21.0)	
Middle school (6–8 years)	311 (14.9)	1012 (15.3)	
High school (9–10 years)	136 (6.5)	671 (10.2)	
Higher secondary (11–12 years)	62 (3.0)	285 (4.3)	
College & above (>12 years)	34 (1.6)	169 (2.6)	
Functional toilet in the house^a^			
Present	6 (0.3)	20 (0.3)	0.917
Absent	2076 (99.7)	6579 (99.7)	
Public tap as source of household drinking water^a^			
Yes	1852 (89.0)	5343 (81.0)	0.693

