The lower than expected baseline prevalence of hookworm infection is a potential limitation of this study and can increase the chance of type I (α) or type II (β) error due to the reduced statistical power to detect the hypothesized effect size [54]. This was unanticipated as the expected prevalence for the sample size calculation was based on an earlier study conducted in the same geographical area (involving a different set of villages) [27]. Given the common ancestry of the population, and similarities in WASH practices, occupation and lifestyle characteristics, this difference in the prevalence of hookworm infection between the present and the earlier study underscores the importance of peridomestic environment in hookworm transmission, which should be investigated further.

The goal of study is to integrate empirical field data with statistical and mathematical modeling to identify the optimal hookworm control strategy that can achieve the greatest impact in the shortest period of time, particularly in settings where long-term program sustainability is a problem. Given the renewed interest in controlling STH infections by 2020, and the commitment towards this effort by governments, donor agencies and pharmaceutical companies alike [55], this study assumes greater importance because of its potential to address some of the major shortfalls of the currently-practiced MDA strategy for STH control.

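### The stated 80% power does not name the proportions compared, is not tied to 12-month prevalence, and is not reached at the observed 18.5% baseline on any reading examined

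*Protocol article*

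**What the plan says.** The Sample size section lists these planning inputs: "38% prevalence of hookworm infection at baseline [27", a 75% cure rate, "reinfection rate of 60% at the end of 1 year [19] in the single cycle group; a minimum effect size of 30" per cent, 80% power, "alpha error of 5" per cent and 10% refusal. It arrives at about 165 per group. With an intra-cluster correlation of 0.06 and 30 people per village it applies a design effect of 2.7 and settles on 450 per group, which it calls adequate.

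Under Outcome measures, "Prevalence and intensity of infection at the end of 12 months after the last MDA cycle is the primary outcome measure". The Statistical analysis section compares prevalence and intensity between the three groups at that time. The section on baseline data and follow-up says the surveys were run as separate cross-sections. The Introduction, by contrast, gives comparison of reinfection rates as the primary objective.

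The Results report that "Three hundred and eighty six (18.5%) of the 2082 participants were positive for hookworm", with a median of 46 people sampled per village. The Discussion calls the low prevalence a limitation that can "increase the chance of type I (α) or type II (β) error due to the reduced statistical power". It gives no revised power.

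**The concern.** Reinfection is defined among people who were infected and then cured. Prevalence in a cross-sectional survey has everyone sampled in its denominator, including people never infected and people not cured. The same effect on reinfection is therefore a smaller absolute difference in prevalence, and a sample sized for the first comparison need not have the same power for the second.

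The inputs do not settle which comparison was meant, so the reader cannot tell what the 80% refers to. Baseline prevalence then came in at about half the planned value. The trial aims to identify the best deworming schedule, so how far a non-significant contrast for two or four cycles can be trusted depends on knowing the real power for the primary outcome.

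**Working it through.** **Method.** Two-proportion normal formula with pooled variance under the null, two-sided 5% (the article does not state sidedness), one pairwise contrast, no multiplicity adjustment. Effective n = n / design effect.

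**1. Reproducing the plan's figure.**
- 60% v 30% at 80% power: 41.97 per arm.
- Divide by the fraction infected and cured, 0.38 × 0.75 = 0.285: 147.3.
- Divide by 0.90 for refusal: 163.6, close to 165.
- Multiply by 2.7 or by 1 + 29 × 0.06 = 2.74: 442 or 448, close to 450.

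This uses every listed input. Other routes come close:
- 22.8% v 11.4% (0.38 × 0.60 and 0.38 × 0.30), one-sided with continuity correction: 151, or 168 after refusal. Two-sided without correction: 170, or 189 after refusal.
- 60% v 42% at an undeclared alpha of 0.025: about 145, or about 161 after refusal.

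**2. Power for 12-month prevalence at the planned 38%.** Effective n runs from 405/2.74 = 148 (450 less 10% refusal) to 450/2.74 = 164.

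Equal uncured fraction in all arms, no new infections:

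| Reading of 30% | Uncured people | Prevalences compared | Power |
|---|---|---|---|
| Absolute, 60% to 30% | stay infected | 0.38(0.25 + 0.75 × 0.60) = 26.6% v 0.38(0.25 + 0.75 × 0.30) = 18.1% | 42-46% |
| Absolute | no separate uncured group | 22.8% v 11.4% | 74-79% |
| Relative, 60% to 42% | stay infected | 26.6% v 0.38(0.25 + 0.75 × 0.42) = 21.5% | 18-19% |
| Relative | no separate uncured group | 22.8% v 16.0% | 32-35% |

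Other assumptions:
- Second dose also cures 75%, independently, so uncured = 0.25² = 6.25%, with 30% absolute: 26.6% v 0.38(0.0625 + 0.9375 × 0.30) = 13.1%, power 84-87%. With 30% relative: 26.6% v 17.3%, power 48-53%.
- Control prevalence returns fully to 38%: a 30% cut (38% v 26.6%) has 55-60% power; a halving (38% v 19%) has 96-97%.

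**3. Power at the observed 18.5%.** 2082/3 = 694 per group; design effect 1 + 45 × 0.06 = 3.70; effective n = 694/3.70 = 188. This assumes that the 12-month survey is as large as the baseline one.

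| Reading | Prevalences compared | Power |
|---|---|---|
| Relative, uncured stay infected | 12.95% v 10.45% | 11% |
| Relative, no separate uncured group | 11.1% v 7.8% | 20% |
| Absolute, uncured stay infected | 12.95% v 8.8% | 25% |
| Absolute, no separate uncured group | 11.1% v 5.55% | 49% |
| Absolute, with second-dose cure | 12.95% v 6.4% | 58% |
| Full return to 18.5%, 30% cut | 18.5% v 12.95% | 31% |
| Full return to 18.5%, halving | 18.5% v 9.25% | 74% |

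As a check on the four-cycle arm, suppose all four doses cure 75% independently (uncured 0.25⁴ = 0.4%) and 30% is absolute. Then 12.95% v 5.6% has 69% power.

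**4. Relative reduction in prevalence detectable with 80% power at effective n 188.**
- Control 18.5%: to 8.6%, a cut of 53%.
- Control 12.95%: to 4.8%, a cut of 63%.
- Control 11.1%: to 3.6%, a cut of 68%.

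**The case against.** The strongest reply is that the compared proportions are nowhere printed. A comparison of 22.8% with 11.4% is a prevalence comparison, matches the primary outcome, and can be brought near 165. This stands: a reader might infer that the trial was sized on the wrong outcome, and the article does not establish that. The reinfection route is only the one that uses every listed input.

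A reader might also infer that 80% is missed even at 38%. That is too strong. The lower figures hold the uncured fraction equal across arms, although the comparison arms are dosed again, and they allow no new infections. Relaxing either, with 30% read as absolute or as a halving, takes power above 80%, and the plainest favourable reading already gives up to 79%.

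Two further inferences fail. Taking 25-49% as the power at 18.5% picks one reading of the 30% and one set of assumptions. Setting a detectable relative cut of 63-68% against 30% mixes scales, because 60% to 30% is itself a 50% relative reduction.

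Finally, the Discussion already concedes reduced power, so it is speculation that a null result would be presented as no benefit. But the concession blames low prevalence alone, gives no size, and leaves the 80% and the claim of adequacy standing. Its mention of type I error is wrong: the significance level is set by the test and does not rise because power falls.

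**Conclusion.** The point holds in a limited form. The Sample size section does not fix what its 80% refers to, and its inputs do not map onto the primary outcome without further assumptions. At 38%, power for 12-month prevalence is about 18-79% with an equal uncured fraction and no new infections, and above 80% only under more favourable assumptions. At the observed 18.5%, no reading examined reaches 80%; the span is 11% to 74%. The detectable relative reduction is about 53-68%, depending on control prevalence.

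These figures rest on the planning correlation of 0.06, baseline survey numbers carried forward to 12 months, and a two-sided 5% test. The cure rate after repeat dosing and the extent of new infection are assumptions, since the article gives neither. The matter should be fixed, but it does not invalidate the design.

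**What to change.** In the Sample size section, name the two proportions compared and say whether 30% is absolute or relative. There and in the limitation paragraph of the Discussion, replace the 80% claim with the power and minimum detectable reduction for 12-month prevalence. Use 18.5% baseline prevalence, 46 per village and the intra-cluster correlation re-estimated from the 2082 baseline participants. Give the result as a range, stating the assumptions on cure after repeat dosing and on new infections. Delete the reference to type I error. State that non-significant contrasts will be interpreted through their confidence intervals.

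This costs a recalculation from data in hand and a few sentences. No enrolment is added; the price is a less favourable stated power.

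### The 450 per group is declared adequate for egg counts as well as prevalence, but the calculation has no egg-count input and the baseline counts do not bear the statement out

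*Protocol article*

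**What the plan says.** Section 2.4 (Outcome measures) says that treatment is judged in two ways: by prevalence, and "quantitatively based on the intensity of infection (fecal egg count"). Both enter the primary endpoint: "Prevalence and intensity of infection at the end of 12 months after the last MDA cycle is the primary outcome measure".

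Section 2.5 (Sample size) starts from a baseline prevalence of 38%, a cure rate of 75%, a "reinfection rate of 60% at the end of 1 year [19] in the single cycle group", and "a minimum effect size of 30%; power of 80%; alpha error of 5%; and 10% refusal rate". It continues: "This requires approximately 165 participants in each group". An intra-cluster correlation of 0.06 for hookworm infection, with 30 people per cluster, gives a design effect of 2.7 and hence 450 per group. That number "was considered adequate to detect effectiveness of the intervention regimes, both qualitatively and quantitatively".

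Section 2.10 (Statistical analysis) acknowledges that egg counts vary widely and follow a negative binomial distribution. Section 3 (Results) reports 386 of 2082 people (18.5%) "positive for hookworm with a mean (SD) intensity of 678 (1649) eggs per gram (epg) of feces". Section 4 (Discussion) names the low baseline prevalence as a limitation that reduces power. It does not treat intensity separately, and the statement in section 2.5 stands unchanged.

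**The concern.** The statement covers two measures, but the calculation covers one. A sample size for a difference in proportions says nothing about power for a mean count unless the spread of the counts is also considered, and helminth egg counts are very dispersed: most people have none and a few have thousands. The correlation used for the design effect is also for infection status, not for counts.

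What is at stake is interpretation. If the 12-month egg counts do not differ significantly, a reader of section 2.5 may take that as evidence from an adequately sized comparison that extra cycles do not lower intensity.

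**Working it through.** **1. The plan's own figure.** Read as a 30% relative reduction in reinfection, the comparison is 0.60 with 0.60 × 0.70 = 0.42. At 80% power:
- two-sided 5% gives 120 per group, or 134 after 10% refusal;
- alpha 2.5% (two comparisons with the single-cycle group, which the text does not state) gives 146, or 163 after refusal, close to 165.

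The design effect is 1 + 29 × 0.06 = 2.74, and 165 × 2.7 = 445.5, so 450 follows from 165. No term for egg counts appears anywhere in this chain.

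**2. Dispersion of counts (section 3).** Take 678 (1649) as the mean and SD among positives and add the zeros, with p = 386/2082 = 0.1854:
- mean = 0.1854 × 678 = 125.7 epg
- variance = 0.1854 × (1649² + 678²) − 125.7² ≈ 573,560, so SD ≈ 757
- CV = 757/125.7 ≈ 6.02 (negative binomial k ≈ 1/CV² ≈ 0.03)

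With the planned p = 0.38 and the same distribution among positives, the mean is 257.6, the SD 1068 and the CV 4.15.

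**3. Power for a 30% lower mean at 450 per group.** The test is a two-sided 5% Wald test of the log ratio of means, with SE = √(2 × CV² × DEFF / 450) and |ln 0.7| = 0.357. The detectable reduction at 80% power is 1 − exp(−2.80 × SE).

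| Prevalence | DEFF | SE | Power, 30% lower mean | Detectable with 80% power |
|---|---|---|---|---|
| 18.5% (observed) | 1 | 0.402 | 14% | 68% |
| 18.5% (observed) | 2.7 | 0.660 | 8% | 84% |
| 38% (planned) | 1 | 0.277 | 25% | 54% |
| 38% (planned) | 2.7 | 0.454 | 12% | 72% |

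At the observed prevalence, 80% power for a 30% reduction would need 2 × 36.3 × 2.80² / 0.357² ≈ 4,480 per group without clustering, and 4,480 × 2.7 ≈ 12,100 with it.

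**4. Other analyses, 30% effect, no clustering to a design effect of about 2.7.**
- Raw means with equal SD: 11% to 7%.
- Ratio of means among positives only (0.185 × 450 ≈ 83 per group): 16% to 8%.
- Log-scale test among positives, assuming lognormal counts: 38% to 17% with 83 positives; 66% to 30% with 0.38 × 450 = 171 positives.
- Cluster-level test of log(count + 1), simulated: 27% to 57% if the effect is 30% fewer infected people; 6% to 7% if only the counts of infected people fall.
- Reading 678 (1649) as describing all 2082 people, which does not fit the wording: 20% to 59% across variants.

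**5. A larger survey.** Baseline samples came from 2082 people, about 694 per group if split equally. The log-ratio test then has power of 20% (DEFF 1) to 10% (DEFF 2.7). This is not the size that section 2.5 calls adequate, but it does not change the picture.

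**The case against.** Several points on the other side are sound.

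- **No arithmetic error.** A reader might infer that the sample size is miscalculated. It is not: 450 follows from 165 and the design effect.
- **Baseline data came later.** A reader might say that the article contradicts itself. The adequacy statement is a planning judgement, and the counts in section 3 were collected afterwards. They show that the statement was not borne out. That it was unsupported follows from the absence of any count input, and using the planned 38% prevalence does not rescue it.
- **The 30% is not stated for counts.** It stands beside the reinfection rate. Applying it to mean egg count is an assumption, although it is the only effect size given and the same calculation is extended to counts. The detectable reductions do not depend on it.
- **No realistic effect is documented.** It is tempting to conclude that the trial has almost no chance of showing any realistic effect on intensity. The documents give no figure for the reduction to expect from two or four cycles against one, and nothing in them rules out reductions of 68% to 84%.
- **The 12-month dispersion is unknown.** Lower prevalence alone would raise the CV, but a smaller spread among positives could offset it. For illustration, 13% positive with a CV of 1.5 among them gives an overall CV of √((1 + 2.25)/0.13 − 1) ≈ 4.9.
- **The Discussion concedes reduced power.** It does so only through low prevalence, and not for intensity. The concession is partial.

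**Conclusion.** The claim of adequacy for egg counts has no calculation behind it, and the trial's baseline counts do not support it. At 450 per group, power for a 30% lower mean count is about 14% to 8% at the observed prevalence and about 25% to 12% at the planned one; the smallest reduction detectable with 80% power at the observed prevalence is about 68% to 84%.

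These figures rest on three assumptions: that the 30% effect applies to the mean count, that dispersion at 12 months equals baseline, and that the design effect for counts lies between 1 and 2.7 (no correlation for counts is given). The exact power depends on the analysis, and log-scale methods give more. The conclusion does not depend on that choice, since none of the analyses tried reaches 80% for a 30% effect.

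A reader might also infer that intensity should be made a secondary outcome. The documents do not require that. Baseline counts are already known, so such a move would itself be a data-informed change of endpoint.

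**What to change.** 1. In section 2.5, confine the adequacy statement to prevalence. Alternatively, replace its egg-count part with the reduction in mean egg count detectable with 80% power (about 68% to 84% at 450 per group), together with the dispersion and design effect assumed.
2. Report the 12-month intensity comparison as a ratio of mean egg counts with a 95% confidence interval.
3. State that a non-significant intensity result will not be read as evidence that extra cycles have no effect on intensity.

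The cost is a few sentences in the protocol and the report. The sample size, the data collected and the primary outcome stay as they are.

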### Identification of villages and participant recruitment

2.6

The villages covered by the Community Health Department of the Christian Medical College (CMC), Vellore, have been mapped, and the geodatabase includes coordinates of each house along with basic socio-demographic data. Additional village-level spatial attributes include the streets, water distribution system, latrines and outdoor defecation areas. This geodatabase was used to identify villages with similar WASH (water, sanitation and hygiene) facilities, proportion of households engaged in agriculture-related activities and proportion of households with domesticated animal(s) for inclusion in the study. Very large villages (population ≥1000), non-rural settlements or villages with non-tribal population were excluded.

The study was initiated after discussions with village leaders and the local administration. Once permission was obtained, a short health educational module about STHs, their transmission and prevention was conducted in each village. A brief description of the study was also provided at the same meeting. Thereafter, the villagers were approached individually for participation and written consents obtained from all participants or their parents/legal guardians.

A person was eligible to participate if he/she was a permanent resident of the village, was aged between 2 and 70 years (both years inclusive), and was willing to provide informed consent and have study personnel visit at home. Individuals with syndromic or serological evidence of HIV infection or immuno-compromise, pregnant women, those with a history of seizure, epilepsy or known neurological disorder, and those with known history of hypersensitivity to albendazole were excluded from participation.

